### Secondary Outcomes

Secondary outcomes for the PWD are changes in the prescription of medication, International Classification of Functioning, Disability, and Health (ICF) scores, mortality rate compared with previous existing records, number of hospitalizations comparing control and intervention groups, and an improvement in physical function and balance.

### Exploratory Outcomes

Some interesting outcomes will be measured with an exploratory aim, but because of their nature as explained ahead, they may not allow for clear conclusions to be drawn. Instead, the purpose of these outcomes is to provide preliminary insights that can be built upon in future studies. These outcomes are as follows: a reduction in depressive symptoms and loneliness, relief from feelings related to the care burden, and improvement in quality of life.

The outcomes regarding depression and relief from feelings related to care burden are measured by means of semistructured interviews. The inclusion of people in later stages of dementia means that there may be challenges in applying these measures to all participants in the study.

A total of 4 months is a short amount of time, and therefore, it is not expected that a large improvement in the quality of life will be observed during this period. However, a small change in the quality of life may provide rationale for future longitudinal studies of the use of SENSE-GARDEN in dementia care, in which quality of life can be examined to a greater extent.

Physiological data will also be collected during the SENSE-GARDEN sessions. The Empatica E4 [20] will be used to collect information on electrodermal activity (EDA) and heart rate. These will be assessed during SENSE-GARDEN visits, as reaction to different stimuli. Data will be collected from a subgroup of participants, depending on their tolerance to use a wristband-mounted device. The device is validated for clinical use. Previous research on nonpharmacological interventions has used the E4 wristband to measure engagement and arousal states in people with mild to moderate dementia [21].

## Methods

### User-Centered Design

To ensure that the SENSE-GARDEN meets the needs of the users, the project has adopted a user-centered design approach to the development of the intervention. This user-centered design process is divided into 3 phases. An overview of the phases is shown in Figure 2.

The first phase focuses on collecting an initial impression of the user experience with nonfunctional low-fidelity prototypes of the SENSE-GARDEN (eg, mock-ups). Small groups of users will be invited to each test site to give their feedback on the overall concept of SENSE-GARDEN. These user groups will include professional care staff, family caregivers, and people living with mild cognitive impairment. Including these individuals at an early stage of the project will ensure that their views are incorporated into the development of SENSE-GARDEN.

The second phase focuses on creating experiences for individual users and aims at gaining a deeper understanding of the users’ needs and requirements. An Alpha version of the SENSE-GARDEN system will be available for this phase of testing. This initial prototype of the SENSE-GARDEN will be tested in a controlled environment. Following the test, a semistructured interview will be conducted with the user to gain a rich insight into their experience.

The third phase involves feasibility testing of the system in the form of pretrials. A small number of users will be recruited at each site (1-2 users). The SENSE-GARDEN test will be tailored to each individual user by using personalized media content, such as family photographs, videos from holidays, and favorite music. The purpose of these tests is to not only ensure that the system works but also define the process of creating individualized experiences for each user.

### Study Design

For the full trials, a controlled before-after study design will be used. The timeline for the study is shown in Figure 3. All participants eligible for the study will receive the SENSE-GARDEN intervention for 3 months. For the final month of the study, half of the participants (the intervention group) will continue to receive the SENSE-GARDEN intervention. The other half of the participants (the control group) will discontinue visits to the SENSE-GARDEN, receiving only normal care. The randomization procedure will use sealed envelopes and will be performed by the local researcher at each test site. The total number of envelopes will be prepared before the recruitment period. A sealed envelope will be assigned to each participant at the time of her or his enrolment. This randomization is to determine whether visits to the SENSE-GARDEN have lasting effects.

The study will start in August 2019, with a recruiting period of 6 months. The intervention period for each participant will be 3 months, followed by 1 month in either the intervention or control condition. The total study period will be 10 months.

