### SENSE-GARDEN Intervention

The study is performed as part of the SENSE-GARDEN EU project, funded by the Active Assisted Living (AAL) Program Call 2016. It is a 3-year project that brings together a consortium of partners across Belgium, Norway, Portugal, and Romania. This multidisciplinary project is embracing a user-centered design approach throughout the development and implementation of the intervention. The SENSE-GARDEN intervention addresses the need for individualized approaches to dementia care by creating a multisensory environment that automatically adapts to the individual with dementia. Through integrating autobiographical music, films, images, and scent with technology, the SENSE-GARDEN is able to offer an immersive experience tailored specifically for the individual based on an individual profile including preferences in music, images, videos, and personal media, such as family photos.

The project aims at creating virtual spaces that are automatically adaptable to the personal memories and individual preferences of the users. The design of the space is shown in Figure 1. These spaces will be designed to strengthen the awareness of older PWDs by combining multisensory stimulation with physical activity and techniques from reminiscence therapy and Montessori methods. This stimulation of sight, touch, hearing, balance, and smell is expected to lead to a reconnection with reality for the PWD, resulting in an improvement in overall well-being and quality of life. The intervention will use a combination of various activities and approaches:

*Reality Wall:* This is the projection of landscape videos, with some including familiar scenery and known places, onto a large wall.*Move to Improve:* This is an augmented reality game aimed at improving balance and increasing levels of physical activity.*Memory Lane:* This is an interactive touchscreen device showing family photographs and media from the individual’s life story.*Life Road:* This is a stationary bicycle placed in front of a film showing a familiar place to the PWD.*Sounds Surround Me:* These are sounds from the surrounding sound speakers playing familiar music and background soundscapes.*Scents to Memories:* This is an olfactory dispensary system releasing familiar scents.*Films of My Life:* This is a collection of classic film excerpts meaningful for the PWD, together with family movies.

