### Recruitment

Participants will be recruited at each study site by a professional caregiver from the SENSE-GARDEN team. The caregivers will inform potential participants about the study with the use of an information leaflet about the project. The potential participants who are interested in the study can then voluntarily express their willingness to participate. The participants who do not express an interest will not be contacted by the project team.

Professional caregivers included in the study will have at least 6 months experience in caring for dementia patients and a background in either nursing, occupational therapy, or physiotherapy or another relevant background when supported by long-term professional experience as a caregiver.

Before the study, the professional caregiver will have a 1-week training in SENSE-GARDEN use. This training comprises guidance on how to collect information from the participant and/or their family members for creating a user profile, upload media contents to the SENSE-GARDEN system, create *workflows* of media contents for individual SENSE-GARDEN sessions, and control the numerous elements in the SENSE-GARDEN space.

Each potential participant will undergo an assessment by a health professional for the evaluation of inclusion and exclusion criteria. For the participants fulfilling the criteria, a randomization to the intervention or control group will be performed.

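### Randomization is done by the local researcher from pre-prepared envelopes assigned at enrolment, 12 weeks before the arms diverge, which leaves allocation concealment weakly protected.

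*Protocol article*

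**What the plan says.** All the allocation steps are in the protocol article, under Study Design and Recruitment.

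- **Who and how:** "The randomization procedure will use sealed envelopes and will be performed by the local researcher at each test site".
- **The set:** "The total number of envelopes will be prepared before the recruitment period".
- **When:** "A sealed envelope will be assigned to each participant at the time of her or his enrolment".
- **Ratio:** for the last month, "half of the participants (the intervention group) will continue to receive the SENSE-GARDEN intervention"; the other half stop visiting.
- **Before that:** "All participants eligible for the study will receive the SENSE-GARDEN intervention for 3 months".
- **Who recruits:** "Participants will be recruited at each study site by a professional caregiver from the SENSE-GARDEN team". A health professional then checks eligibility, and "For the participants fulfilling the criteria, a randomization to the intervention or control group will be performed".

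The Participants section gives site totals of 25 (Belgium), 15 (Norway) and 15 (Portugal), 55 in all. Study Design gives the purpose of the randomization: to learn whether effects persist once visits stop.

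The article does not say whether there is one envelope set or one per site, whether a set is balanced within a site, or when an envelope is opened. It does not say that the local researcher knows the contents, or that this person also recruits.

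**The concern.** The criticism is of a choice that the article states: a person at the site carries out the allocation from physical envelopes prepared in advance. The two arms cannot be masked from site staff, because visits either go on or stop. In that setting, concealment protects the comparison only if nobody who can influence enrolment can learn or alter the next allocation. A local holder of envelopes can open one early or pick among them. No tallying is needed for that.

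The early timing adds exposure for no gain. The allocation has no use until week 12, yet it is fixed to the participant at enrolment.

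At stake is the comparison between continuing and stopping from T2 (week 12) to T3 (week 16). Everyone receives the intervention up to T2, so the change from T0 to T2 is a single-group before-after comparison. The last month is the only part with a randomized control. With 55 participants there are 27 or 28 per arm, so a few steered allocations could matter.

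**Working it through.** The article gives no figure for predictability, so there is none to reproduce. The check asks how much a person who only counts past allocations could predict.

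**Inputs from the article:** site totals 25, 15 and 15; half to each arm; a set prepared in advance.

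**Assumptions not in the article:** (i) one near-balanced set per site, 13/12, 8/7 and 8/7; (ii) each envelope is opened at enrolment; (iii) the guesser always names the arm with more envelopes left.

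**Correct guesses.** With *a* and *b* envelopes left, the expected number of correct guesses is

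E(a,b) = max(a,b)/(a+b) + [a/(a+b)]·E(a−1,b) + [b/(a+b)]·E(a,b−1), with E(0,0) = 0.

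For a set of N and N−1 this reduces to N − 1 + 4^N / [2·C(2N,N)]:

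- 13/12: 12 + 67,108,864/(2 × 10,400,600) = 15.23 of 25, or 60.9%.
- 8/7: 7 + 65,536/(2 × 12,870) = 9.55 of 15, or 63.6%.
- Three sites: 15.23 + 9.55 + 9.55 = 34.3 of 55, or 62.4%. Chance gives 27.5, so the gain is 6.8 guesses.

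**Allocations known with certainty.** Once one arm is used up, the rest are known. The expected number is a/(b+1) + b/(a+1):

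- 13/12: 13/13 + 12/14 = 1.86.
- 8/7: 8/8 + 7/9 = 1.78.
- Three sites: 1.86 + 1.78 + 1.78 = 5.4 of 55, or 9.8%.

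**Changing the assumptions.**

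| Situation | Correct guesses | Known with certainty |
|---|---|---|
| Set balanced within each site, opened at enrolment | 62.4% | 5.4 of 55 |
| One common 28/27 set, opened at enrolment | 31.7 of 55 = 57.7% | 28/28 + 27/29 = 1.9 of 55 |
| Sets not balanced within site | towards 50% | fewer |
| Sealed until week 12 | towards 50% | fewer |

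The common-set row also needs the guesser to know the allocations at all three sites. In the last row no tally exists for the first 12 weeks of recruitment. Taking the 6-month recruitment period as 26 weeks, that is 12/26, or 46%, of it. After that the tally lags by 12 weeks.

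**Route from knowledge to bias.** Under Study Design the local researcher allocates. Under Recruitment a professional caregiver approaches participants and a health professional judges eligibility. For enrolment to be steered, what the researcher knows must reach one of the other two.

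**The case against.** The strongest case on the other side has four parts.

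*A reader might infer that the next allocation can be predicted and that one site person both sees it and decides who enters.* The documents do not support this. Balance within site and opening at enrolment are assumptions. An envelope may be assigned at enrolment and stay sealed until week 12, which would come close to the timing recommended here. Recruitment and eligibility are given to other roles. At small sites information may well pass between them, but the article does not say so. Even on the least favourable assumptions, only about 5 of 55 allocations are certain. This objection stands, and it limits the point to weak protection of concealment.

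*The motive is thin.* At enrolment nobody has had a trial session, so a wish to continue is hard to judge. In addition, T0, T1 and T2 precede the split, so imbalance in measured outcomes would be visible and could be adjusted for. This stands in part: unmeasured differences, such as family engagement, cannot be adjusted away.

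*The reach is limited.* Steering between arms cannot bias the pooled change from T0 to T2, which bears on the main aim of improving well-being. This stands.

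*Details such as opacity, numbering and the preparer of the envelopes may be in a fuller protocol.* This also stands, and their absence is not held against the article. Who performs the allocation, by what means and at what time of assignment is stated, and that is what the point rests on.

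**Conclusion.** The point holds in limited form. The article places allocation in the hands of the local researcher, using pre-prepared envelopes assigned 12 weeks before they are needed, and describes no independent step. That protects concealment weakly, mainly because the holder could open or select envelopes.

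Counting is a secondary and conditional risk: about 62% correct guesses if sets are balanced within site and opened at enrolment, 57.7% for one common set, and nearer 50% if sets are unbalanced or stay sealed until week 12. The documents do not show that enrolment will be steered. If it were, the damage would be confined to the randomized T2 to T3 comparison. The change is worth making because that is the study's only randomized contrast and the remedy is cheap.

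**What to change.** Move the allocation off site and later in time.

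1. Let a consortium partner without a trial site hold the list. The project "brings together a consortium of partners across Belgium, Norway, Portugal, and Romania", and the trial sites are in Belgium, Norway and Portugal only, so a Romanian partner could do this.
2. Stratify the list by site, with randomly varying block sizes that are not disclosed to the sites.
3. Release each allocation to the local researcher by message, only after the participant has been registered and the T2 assessments are complete. The local researcher receives the result and does not produce it.
4. Replace the envelope sentences under Study Design, and align the Recruitment sentence that places randomization directly after the eligibility check.

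Late release also means that nobody can know the arm during the shared 3 months. The cost is one list and at most 55 messages, with minor coordination and a short wait around week 12. Participants lost before T2 would not be randomized, so the number allocated may fall below 55.

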### Study Procedures

During the 3 months of the intervention period, the PWD will visit the SENSE-GARDEN on an average of 3 times per week. Each participant should visit the SENSE-GARDEN a minimum of 25 times during the intervention period. Any participant who visits less than 25 times will be considered a dropout. On each visit to the SENSE-GARDEN, the PWD is accompanied by 1 caregiver (formal or informal). It is desirable that approximately one-third of the visits are performed with an informal caregiver.

Logs of interaction with the system will be collected continuously, including visit time and duration and system feedback given by the caregivers (through a tablet interface).

Observations will be made at 3 of the SENSE-GARDEN sessions during the intervention period. During this time, measurements on social presence and physical activity will be collected. Video recording will be required during the 3 observation sessions. The recordings will solely be used for data analysis and will not be shared. They will be accessible only to authorized researchers in charge of data analysis. Video recordings will only be made during sessions involving participants that have given their informed consent to being recorded.

For the control period, visits from the family will be logged during normal care.

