##### Person With Dementia

###### Primary Outcomes

####### A Reduction in Behavioral and Psychological Symptoms in Dementia

The Bedford Alzheimer Nursing Scale–Severity (BANS-S) [25] and the Cohen–Mansfield Agitation Inventory (CMAI) [26] will be used to determine whether the intervention reduces behavioral and psychological symptoms of dementia. BANS-S is a nursing staff–administered questionnaire that assesses dressing, sleeping, speech, eating, mobility, muscles, and eye contacts in persons with severe dementia. It is a reliable measure with good internal consistency (Cronbach alpha=.64-.80). CMAI is a widely used tool that evaluates aggressive behavior, nonaggressive behavior, and verbally aggressive behavior. The caregiver-rated questionnaire comprises 29 agitated behaviors, each rated on a 7-point scale of frequency ranging from 1 (never) to 7 (several times an hour).

####### Increase in the Feeling of Social Presence

Observational measures will be used to determine the level of social engagement in the participants with dementia. These tools will be the Observed Emotion Rating Scale (OERS) [27], the Verbal and Nonverbal Interaction Scale (VNVIS-CR) [28], and the Observational Measurement of Engagement (OME) [29]. All 3 measures have previously been used in studies observing people living with dementia. OERS assesses pleasure, general alertness, anxiety or fear, and sadness at 10-min intervals. VNVIS-CR is a tool developed specifically to measure verbal and nonverbal interaction in people with mild to moderate dementia. The 26 items assess nonverbal social behaviors, nonverbal unsociable behaviors, verbal sociable behaviors, and verbal nonsociable behaviors. The OME evaluates various dimensions of engagement in people with mild to severe dementia. The tool measures attention to stimulus, attitude toward stimulus, rate of refusal, duration, and activity.

Observations will be made during at least 2 of the SENSE-GARDEN sessions for each participant. For participants in the intervention group, recordings will be taken during a SENSE-GARDEN session in week 4, week 12, and week 16. Participants randomized to the control group will only have recordings taken during a session in week 4 and week 12, as these individuals will no longer be visiting the SENSE-GARDEN after week 12.

####### Improvement in Cognitive Function

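### Participants are randomised at enrolment although the arms do not differ until after week 12, so every loss in the common phase falls after randomisation in the trial's only randomised comparison

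*Protocol article*

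**What the plan says.** All references are to the protocol article.

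- **When allocation happens.** Study Design: "A sealed envelope will be assigned to each participant at the time of her or his enrolment". Recruitment puts it directly after the eligibility check: "For the participants fulfilling the criteria, a randomization to the intervention or control group will be performed". The Abstract also has all eligible participants randomised.
- **Who does it.** Study Design: "The randomization procedure will use sealed envelopes and will be performed by the local researcher at each test site". All envelopes are prepared before recruitment starts.
- **When the arms part.** Study Design: "All participants eligible for the study will receive the SENSE-GARDEN intervention for 3 months". The arms differ only in the final month. Outcome Measures (Primary Outcomes, social presence) says that control participants have no week 16 session recording, "as these individuals will no longer be visiting the SENSE-GARDEN after week 12".
- **What randomisation is for.** Study Design: "This randomization is to determine whether visits to the SENSE-GARDEN have lasting effects".
- **What counts as a loss in the common phase.** Study Procedures: "Any participant who visits less than 25 times will be considered a dropout". The count runs over the 3-month intervention period, in which "the PWD will visit the SENSE-GARDEN on an average of 3 times per week".
- **Who attends and who rates.** Under Study Procedures a formal or informal caregiver is present at each visit. Under Outcome Measures the CMAI is rated by a caregiver, the BANS-S is administered by nursing staff, and the Zarit Burden Interview is the family caregiver's own report.

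The article does not say when an envelope is opened, who is told the result, or that anyone is kept unaware of the arm during the first 12 weeks. It gives no reason for allocating before the common phase.

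**The concern.** The question that randomisation is meant to answer begins at T2 (week 12), but the allocation is made at entry. The gap has two consequences.

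First, it turns losses that need not concern the randomised comparison into post-randomisation losses. Residents with moderate to severe dementia may die, fall ill, refuse sessions or fall short of 25 visits during the common phase. Had they left before being randomised, they could not disturb the comparison of arms. As planned, they have already been allocated, and whoever remains at week 12 is a subset of the randomised groups.

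Second, if the allocation becomes known before week 12, that subset and its ratings could depend on the arm. A caregiver who knows that a resident will stop at week 12 might put more or less effort into attendance, which feeds straight into the 25-visit count, or might score T1 and T2 differently.

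The lasting-effect comparison is the only contrast in this before-after design that randomisation protects, so it is worth keeping that protection whole.

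**Working it through.** The plan states no figure on this point. The check sets the timings side by side and then asks what the timing costs and what moving it would gain.

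**1. Length of the gap.** Allocation is at T0 and divergence follows T2 at week 12, with final follow-up at week 16. Share of follow-up between allocation and divergence: 12/16 = 75%.

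**2. Where the dropout rule acts.** At 3 visits a week, the common phase has 3 × 12 = 36 visits (12 weeks) to 3 × 13 = 39 visits (13 weeks). The threshold of 25 is 25/36 = 69% to 25/39 = 64% of plan. The rule therefore acts entirely between randomisation and divergence.

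**3. Numbers left at week 12.** The article gives no loss rate, so 0 to 30% is assumed. Power is for a two-sided t-test at 0.05 with d = 0.5, the article's medium effect: noncentrality d × √(n1·n2/(n1+n2)), degrees of freedom n1 + n2 − 2.

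| Assumed loss before week 12 | Left of 55 | Arms if even | Power |
|---|---|---|---|
| 0% | 55 | 28 / 27 | 0.444 |
| 10% | 50 | 25 / 25 | 0.410 |
| 20% | 44 | 22 / 22 | 0.367 |
| 30% | 38 | 19 / 19 | 0.323 |

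These losses occur whenever the envelope is drawn, so later randomisation recovers none of this power. To have 55 at week 12, enrolment would have to be 55/0.9 → 62, 55/0.8 → 69 or 55/0.7 → 79 at 10, 20 or 30% loss. The gain from later randomisation is in validity: the same losses become pre-randomisation losses.

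**4. Does early allocation matter through unequal arm sizes?** Hardly. With 44 left, 22 v 22 gives power 0.367 and 25 v 19 gives 0.362, a difference of about half a percentage point.

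**5. Does a later draw by itself even out the arms?** No. Take 28 and 27 envelopes and independent retention of 80%. Under allocation at entry, the chance that the arms differ by 5 or more is P(|X − Y| ≥ 5) with X ~ Bin(28, 0.8) and Y ~ Bin(27, 0.8), which is 0.14; at 70% retention it is 0.19. If those remaining at week 12 instead draw from the same unblocked stack of 55, the chances are again 0.14 and 0.19, because the thinning is the same. Near-equal arms need blocked envelopes within site.

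**6. Foreknowledge.** This depends on a step that the article leaves open:
- *Envelope stays sealed until week 12:* early losses and T1/T2 ratings cannot depend on knowledge of the arm. The cost is mainly precision and chance imbalance.
- *Envelope opened earlier:* attendance, the 25-visit count and the T1/T2 ratings can all depend on the arm, and bias is possible. Its size cannot be computed from the documents.

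**The case against.** The strongest reply is that a sealed envelope assigned at enrolment need not be opened then. If it stays sealed until week 12, no one has foreknowledge and early losses are unrelated to the arm. The article is also condensed, and its timeline figure is not available here. This stands as far as it goes: a reader might infer that staff know the arm for 3 months, but the text supports only that they could. It does not remove the point. Recruitment describes randomisation as carried out once eligibility is met, no delay in opening is stated, and those lost early would still have been randomised.

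Other stronger readings are tempting and not supported:

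- *T0 ratings are contaminated.* The order of the T0 assessment and allocation is not given. Only T1 and T2 clearly follow allocation.
- *Participants with fewer than 25 visits are excluded from analysis.* The article calls them dropouts but does not say that they leave the analysis, and analysis sets may be defined elsewhere.
- *Early allocation leaves damagingly unequal arms.* Steps 4 and 5 show that such imbalance costs almost no power, and that a later draw without blocking does not prevent it.
- *The main objective is undermined.* Change over T0 to T2 concerns people who are all treated alike. Only the lasting-effect question depends on randomisation.

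It is also fair to say that the change leaves T3 unblinded, since caregivers will see who has stopped, and that randomising at week 12 restricts the question to people who reach week 12.

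**Conclusion.** The point holds, with limited reach. As written, allocation comes 12 weeks before the arms differ, for a randomisation whose only stated purpose is the lasting-effect question. All losses in that period, including those created by the 25-visit rule, are post-randomisation losses in that comparison. This follows from the text without assumptions.

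That knowledge of the arm biases attendance or the T1 and T2 ratings is possible but conditional on envelopes being opened before week 12, which the article neither states nor rules out. The number of people affected rests on an assumed loss rate: 55 − 50 = 5 at 10%, 55 − 44 = 11 at 20%, 55 − 38 = 17 at 30%. No size can be put on the bias.

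It should be changed because the remedy is cheap and the randomised comparison has no other protection against early losses. It does not invalidate the trial's main before-after question.

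**What to change.** Amend the randomisation sentences in Study Design and Recruitment so that:

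1. the envelope is drawn and opened at week 12, after all T2 assessments are recorded, among participants still in the study;
2. envelopes are prepared in blocked order within each site, keeping the 1:1 ratio;
3. everyone randomised at that point is analysed by allocated arm;
4. the text says how the 25-visit label bears on being still in the study at week 12, so that any attendance condition is settled before the draw.

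If allocation at enrolment is kept, the article should at least state that envelopes stay sealed until the T2 assessments are complete, and that all randomised participants are analysed whatever their visit count. That removes the foreknowledge but leaves early losses after randomisation.

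**Cost.** A change to a few sentences and to the preparation of the envelopes, with no extra visits or staff and no change to what either arm receives. Families learn the assignment for weeks 12 to 16 later, and the randomised question then applies to participants who reach week 12. Lost participants are not recovered, and the T3 assessment is no better blinded than before.

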### Objectives

The study will test operational SENSE-GARDENs installed in the 3 study sites: Belgium, Norway, and Portugal. With these countries, a large coverage of the European context is achieved, allowing to study cultural, social, economic, and legal differences between the countries and European regions. The primary objective of this study is to determine whether the delivery of the innovative technology developed in SENSE-GARDEN can improve well-being in older adults with intermediate to advanced dementia. The WHO defines health as the “state of complete physical, mental, and social well-being and not merely the absence of disease or infirmity” [19]. This study will adopt this holistic approach to health and well-being by measuring well-being through primary outcomes related to behavior, activities of daily living, cognitive function, quality of life, self-identity, communication, and social presence.

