#### Outcome Measures

The following measures will be applied at baseline (T0), 4-week follow-up (T1), 12-week follow-up (T2), and a final follow-up at 16 weeks (T3). An overview of these measures is given in Table 1.

**Table 1 table1:** Overview of outcome measures.

Outcome		Measurement	Timepoint

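### The efficacy objective has no concurrent comparator before week 12, and the only randomised contrast (continue versus stop at week 16) cannot by itself show a lasting effect

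*Protocol article*

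**What the plan says.** The Objectives section makes efficacy primary: "The primary objective of this study is to determine whether the delivery of the innovative technology developed in SENSE-GARDEN can improve well-being". Study Design states that "a controlled before-after study design will be used" and then sets the exposure: "All participants eligible for the study will receive the SENSE-GARDEN intervention for 3 months". The arms separate only afterwards: "For the final month of the study, half of the participants (the intervention group) will continue to receive the SENSE-GARDEN intervention", while "The other half of the participants (the control group) will discontinue visits to the SENSE-GARDEN, receiving only normal care". The purpose given for this allocation is persistence: "This randomization is to determine whether visits to the SENSE-GARDEN have lasting effects".

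Outcome Measures sets assessments at baseline (T0) and weeks 4, 12 and 16 (T1, T2, T3). Data Analysis plans a repeated measures ANOVA over T0-T3 to look for an effect over time. It states over 80% power for 55 people and a medium difference at the 0.05 level. Elsewhere in that section a medium effect is d = 0.5, and the article says earlier literature cannot supply a clinically meaningful difference. The Limitations section names the small sample and variation between sites. It does not mention the lack of a comparator up to T2.

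**The concern.** The word controlled, set beside an efficacy objective, suggests that improvement under the intervention will be compared with what happens without it. Up to T2 nobody is without it. A shift in ratings caused by extra attention, by raters' expectations or by the passage of time cannot be separated from an intervention effect. Disease progression could equally hide a real benefit.

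The one randomised comparison is given a different job. When continuing is compared with stopping, a lasting effect means that the stopped arm stays level with the continued arm. Two arms that never benefited are also level. If level arms were taken as persistence, and a T0-T2 shift as efficacy, both main conclusions could be reported for an intervention that does nothing.

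**Working it through.** **Inputs.** From the article: N = 55, halves of 27 and 28, d = 0.5, alpha 0.05. Assumed: two-sided testing, no dropout, SD = 1, and a T2-T3 correlation rho, because the article gives none.

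**1. The plan's own power figure.** Take all 55 as one group with a standardised within-person change of 0.5. The noncentrality is 0.5 × √55 = 3.71 and the critical t(54) is 2.005, so power is 95%. If d is instead scaled by the raw SD, power is 73% at a correlation of 0, 87% at 0.3 and 95% at 0.5. A four-time-point repeated measures ANOVA at f = 0.25 gives 88% at correlation 0 and more above that. The stated figure of over 80% is thus reproduced for a change over time, except when the paired calculation is scaled by the raw SD at very low correlation.

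**2. What that change can be attributed to.** Suppose the intervention does nothing, but scores drift by δ SD of change. The noncentrality is δ × √55.

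| Drift δ | Noncentrality | P(significant T0-T2 change) |
|---|---|---|
| 0.2 | 1.48 | 31% |
| 0.3 | 2.22 | 59% |
| 0.4 | 2.97 | 83% |

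**3. The randomised contrast at T3.** SE = √(1/27 + 1/28) = 0.270 SD. Unadjusted noncentrality is 0.5/0.270 = 1.85 and the critical t(53) is 2.006, so power is 44%. The 95% CI half-width is 2.006 × 0.270 = 0.54 SD. Adjusting for T2 divides the effect, and multiplies the half-width, by √(1 − rho²), respectively raising and narrowing them.

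| Analysis | Noncentrality | Power at d = 0.5 | 95% CI half-width |
|---|---|---|---|
| Unadjusted | 1.85 | 44% | 0.54 SD |
| Adjusted, rho 0.5 | 2.14 | 56% | 0.47 SD |
| Adjusted, rho 0.7 | 2.60 | 72% | 0.39 SD |
| Adjusted, rho 0.8 | 3.09 | 86% | 0.32 SD |

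**4. What a non-significant T3 difference distinguishes.**

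- Intervention inert: non-significant in 95% of trials.
- Effect real and fully persistent: the true T3 difference is again zero, so again 95%.
- Medium effect fully lost within the month: non-significant in 1 − 0.44 = 56% unadjusted, 44% at rho 0.5 and 28% at rho 0.7.

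The first two cases cannot be told apart by this comparison at any sample size or correlation. The third is missed often unless rho is high.

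**5. Outcomes with no T3 contrast.** Social presence is observed, and self-awareness and engagement are recorded, during SENSE-GARDEN sessions (Table 1). The control arm has no sessions after week 12, and the outcome text limits its recordings to weeks 4 and 12. For these primary outcomes no randomised comparison exists at T3.

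**The case against.** The article nowhere says that similar arms at T3 will be read as a lasting effect. It states a purpose and plans an ANOVA over all four time points. On that plan the natural picture of persistence is improvement by T2 that the stopped arm then keeps, and an inert intervention would not give that picture unless scores also drifted upwards. This stands. The rule is one a reader might infer, and it cannot be charged to the article as written. The picture of gain followed by maintenance does not rescue the inference, however, because both the gain and the maintenance are uncontrolled within-group changes.

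A reader might also infer that the design says nothing controlled about efficacy. That goes too far. A clear T3 difference in favour of continuing would be randomised evidence that continued visits help, although it would count against full persistence.

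Two specific bias claims are tempting but not supported. The article is silent on masking: caregiver and staff ratings make expectation effects plausible, but open rating is not documented. Regression to the mean is weakly supported, because eligibility is set by age and dementia stage and not by a threshold on the outcome scales. Progression would tend to mask benefit more than to mimic it.

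Finally, the treated-by-all phase is openly described, and a decision rule or margin may sit in a fuller document. That is fair as to the margin. No analysis plan, however, can supply a comparator for T0-T2.

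**Conclusion.** The point holds in this form. The primary objective is efficacy, the arms are treated alike until T2, and the T0-T2 change is uncontrolled despite the design label. The randomised T3 contrast is assigned to persistence, which similarity between arms cannot establish alone.

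The size depends on assumptions. The 59% figure assumes a drift of 0.3 SD of change; the article gives no estimate of drift, and 0.2 to 0.4 gives 31% to 83%. Power of 44% and a half-width of 0.54 SD apply only to an unadjusted T3 comparison. Adjusting for T2 gives about 56-72% at rho 0.5-0.7, and 86% at 0.8. It would therefore be wrong to say that a null T3 result can never exclude a medium difference: at rho 0.7, an estimate within about 0.5 − 0.39 = 0.11 SD of zero would do so. The stated power is not an arithmetic error; it belongs to a change that cannot be attributed to the intervention.

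**What to change.** - Describe the design as an uncontrolled 3-month phase followed by randomised withdrawal.
- Report T0-T2 change as uncontrolled and not by itself evidence of efficacy, and add this to the Limitations.
- Make the T3 difference between continuing and stopping, adjusted for T2, the controlled evidence of effect for outcomes measured in both arms at T3. State that this excludes the session-based outcomes (social presence; self-awareness and engagement).
- Report a non-significant T3 difference as inconclusive, with its confidence interval. Keep any statement about lasting effects descriptive, since the stopped arm's own course from T0 to T3 is also uncontrolled.

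**Cost.** Wording and reporting only; no new visits or measurements. The claims become more modest, and this sample is unlikely to confirm persistence. With a true T3 difference of zero and an illustrative margin of 0.5 SD, the 95% CI would lie inside the margin in about 2% of simulated trials unadjusted, 13-14% at rho 0.5 and 44% at rho 0.7. A formal margin is therefore not proposed as a test here.
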